## Abstract

**Background:**

The incidence of postoperative pancreatic fistula following distal pancreatectomy is as high as 30%-50%. Postoperative pancreatic fistula can be a major cause of perioperative morbidity, resulting in prolonged hospital stays and increased health care costs. The management of the pancreatic stump is one of the key factors influencing the occurrence of postoperative pancreatic fistula after distal pancreatectomy, but the optimal management approach remains debatable. The main methods for pancreatic stump closure include manual suturing and stapler closure. However, both methods are associated with a high risk of postoperative pancreatic fistula, which may be related to the balance between providing sufficient pancreatic duct burst pressure and ensuring blood supply to the stump. Ligation of the pancreatic stump has been attempted to reduce the risk of postoperative pancreatic fistula following distal pancreatectomy, but its efficacy remains limited by the challenge of achieving the optimal ligation force.

**Objective:**

This study aims to investigate whether ligation of the pancreatic stump with a quantified force can decrease the risk of postoperative pancreatic fistula following distal pancreatectomy.

**Methods:**

In this nonrandomized controlled clinical study at a tertiary center in China, the major eligibility criterion is the presence of lesions planned for distal pancreatectomy. Sixty patients will be allocated to the experimental or control group according to their choice. Recruitment for either group will be discontinued upon reaching the predefined sample size of 30 participants. In the experimental group, the pancreas will be ligated 5 mm from the pancreatic stump with a quantified force to provide a pancreatic duct burst pressure of approximately 40-70 mm Hg. The ligation force will be provided by a 3.2-mm-diameter silicone ring. During pancreatic stump ligation, this silicone ring will be stretched to 15 mm, generating an applied force of 1.3 N. The pancreas will be severed using energy-based devices before or after the ligation. In the control group, the pancreatic stump will be managed by manual suturing or stapling closure according to the surgeon’s clinical judgment and preference. Postoperative regular follow-up examinations will be conducted. The primary outcomes include postoperative pancreatic fistula and postoperative hospital stay, and the secondary outcomes include intra-abdominal infection, incision infection, and postoperative treatment costs. The primary and secondary outcomes of patients in this cohort will be statistically compared using appropriate tests.

**Results:**

This study started in February 2025, and the recruitment period is from February to September 2025.

**Conclusions:**

This protocol proposes a novel approach for pancreatic stump management aimed at preventing postoperative pancreatic fistula following distal pancreatectomy. The research team established the optimal ligation force for the pancreatic stump to ensure adequate burst pressure for the pancreatic duct while preventing acute stump necrosis, thereby theoretically reducing the risk of postoperative pancreatic fistula.

**Trial Registration:**

Chinese Clinical Trial Register ChiCTR2500097781; https://www.chictr.org.cn/showproj.html?proj=247008

**International Registered Report Identifier (IRRID):**

DERR1-10.2196/74018

## Introduction

Distal pancreatectomy is the primary surgical procedure for treating inflammatory lesions as well as benign and malignant tumors in the pancreatic body and tail. Postoperative pancreatic fistula (POPF) is a common and severe complication of distal pancreatectomy, with an incidence rate of approximately 30%-50% [1,2]. POPF can lead to delayed gastric emptying, intestinal obstruction, hemorrhage, wound infection, intra-abdominal abscess, and sepsis. These complications can further increase hospital stay and medical expenses and may potentially result in death [3,4].

To reduce POPF, surgeons have explored numerous strategies, with the aim of achieving better outcomes through improved patient management and advanced techniques [5-10]. The closure technique used for the stump is a crucial factor influencing the occurrence of POPF, and 2 methods are primarily used at present: manual suturing and stapling closure [5,6]. Stapling devices are often used due to their simplicity and convenience, but they may not effectively close the pancreatic stump when the pancreas is hard or thick. In such cases, manual suturing is often the sole option. Additionally, surgeons have investigated techniques such as wrapping the stump with mesh [7], saline-coupled radiofrequency ablation [10], pancreaticojejunostomy [9], preoperative pancreatic duct stenting [11,12], and the application of fibrin patches to the stump [8]. Unfortunately, none of these techniques have significantly reduced the risk of pancreatic fistula. In their expert consensus on the management of the pancreatic stump during distal pancreatectomy in 2022, the International Study Group on Pancreatic Surgery stated that both manual suturing and stapling closure have their respective advantages, and both methods are associated with an equal risk of pancreatic fistula. The use of energy devices or additional biomaterials to seal the pancreas or the combined use of these methods also does not reduce the incidence of pancreatic fistula [13].

Closure of the main pancreatic duct (MPD) is a key step to prevent pancreatic fistula. However, stapling closure may not provide a sufficiently high burst pressure for the pancreatic duct, even when the pancreatic stump is adequately closed. Under physiological conditions, the pancreatic duct pressure ranges from 3 to 31 mm Hg [14,15], but the burst pressures provided by approximately half of the stapling devices for pancreatic duct closure are below 31 mm Hg [16,17], leading to pancreatic fistula in some patients. Manual suturing can provide a burst pressure of up to 400 mm Hg for the pancreatic duct through sutures, but the high pressure on the tissue can cause tissue necrosis and new pancreatic duct proliferation, resulting in pancreatic fistula [17]. Additionally, identification of MPD can be difficult after pancreatic transection in some patients, and empirical suturing increases the risk of pancreatic fistula.

Ligating the pancreatic stump is another technique for the closure of the pancreatic stump. Ligation of the pancreatic tissue proximal to the stump can provide sufficient burst pressure for the pancreatic duct. However, ligation may also lead to acute tissue necrosis and pancreatic duct regeneration, similar to suturing [18]. To address this issue, the project applicant quantified the ligation force to achieve a burst pressure of approximately 40-70 mm Hg for the pancreatic duct. This burst pressure is much higher than the maximum pressure of the pancreatic duct under physiological conditions but lower than the average arterial pressure under physiological conditions. Therefore, theoretically, the use of this burst pressure can avoid the direct leakage of the pancreatic juice from the pancreatic duct while reducing the risk of pancreatic stump acute necrosis by providing partial blood supply to the pancreatic stump, preventing POPF caused by the necrosis-proliferation process of the pancreatic stump.

Thus, we hypothesized that the rate of POPF in patients who undergo pancreatic stump ligation with a quantified force would be lesser than that using other closure techniques. To validate this hypothesis, we launched this clinical trial. According to the Evidence Map of Pancreatic Surgery, this is the first trial of its kind [19].

## Methods

### Study Design

The methods have been designed and are reported according to the SPIRIT (Standard Protocol Items: Recommendations for Interventional Trials) reporting guidelines (Multimedia Appendix 1) [20].

### Study Setting

This nonrandomized controlled clinical study is being conducted at a tertiary center in China. The study population consists of patients who are scheduled to undergo distal pancreatectomy. Experienced surgeons will determine the eligibility of the patients and obtain informed consent from the patients (see online supplemental materials). An overview of the protocol is shown in Figure 1.

**Figure 1 figure1:**
[figure not shown]
Flowchart of the study.

### End Points

#### Primary End Points

The primary end points are POPF and postoperative hospital stay.

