### Statistical Methods

#### Hypothesis

##### Null Hypothesis

The rate of POPF in patients who undergo pancreatic stump ligation is not lesser than that using other closure techniques.

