##### Alternative Hypothesis

The rate of POPF in patients who undergo pancreatic stump ligation is lesser than that using other closure techniques.

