#### Sample Size Calculation

Based on published clinical studies on the incidence of pancreatic fistula [6-8] using other closure techniques, the incidence of POPF was set at 40%. On the basis of the results of previous animal experiments, the expected incidence of POPF in the ligation strategy is 5%. Using the formula *n = 2p̅q̅(Z_α_+Z_β_)^2^/(p1-p2)^2^* for sample size calculation with the probability of type I error of .05 and the statistical power of .90, we estimated that 30 participants should be included in each group.

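### Two unranked primary end points are declared, but the hypotheses, alpha and sample size cover POPF only; POPF should be the sole primary or be tested first

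*Protocol article*

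**What the plan says.** The article gives primary status to two outcomes, in two places. The Primary End Points section reads "The primary end points are POPF and postoperative hospital stay", and the Methods part of the abstract reads "The primary outcomes include postoperative pancreatic fistula and postoperative hospital stay". Neither place ranks them or says whether one or both must succeed.

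The confirmatory content concerns POPF only:

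- Hypotheses: the alternative reads "The rate of POPF in patients who undergo pancreatic stump ligation is lesser than that using other closure techniques", and the null is its complement, again for POPF alone.
- Sample Size Calculation: POPF rates of 40% (control) and 5% (ligation), "with the probability of type I error of .05 and the statistical power of .90", giving 30 per group.

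For hospital stay, the Definitions section says what is measured (day of surgery to discharge). The article gives no hypothesis, effect size, standard deviation or power for it. The abstract says only that the outcomes will be compared with appropriate tests, and the Statistical Analysis section gives no testing order, alpha split or success rule.

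**The concern.** The end-point section treats hospital stay as equal to POPF, while the hypotheses and sample size are written as if POPF were the only primary. The trial's criterion for success is therefore open. As written, a non-significant POPF result with a shorter stay could be reported as a positive primary result, although no stated hypothesis covers it. Conversely, if both end points are needed, the quoted power is not the power of the trial.

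The open criterion matters more here because the Limitations section foresees a data-driven decision on enlarging the sample. What counts as success should be settled before any outcome is compared.

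**Working it through.** **Inputs from the article.** Control POPF rate p1 = .40; ligation rate p2 = .05; alpha .05 (sidedness not stated); power .90; 30 per group. The formula is the article's own: n = 2·p̄·q̄·(Zα+Zβ)²/(p1−p2)².

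**Inputs assumed here.** The correlations between the two test statistics and the standardised effects for hospital stay. The article gives neither.

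**1. Reproducing 30 per group.** p̄ = (.40+.05)/2 = .225, q̄ = .775, 2·p̄·q̄ = .34875, (p1−p2)² = .1225.

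- Two-sided .05: .34875 × (1.960+1.282)²/.1225 = 29.91, so 30. This matches.
- One-sided .05: .34875 × (1.645+1.282)²/.1225 = 24.4, so 25. This does not match.

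So the sample size uses two-sided .05 (equivalently one-sided .025), all of it on POPF. By the same formula, power at 30 per group is Φ(√(30 × .1225/.34875) − 1.960) = Φ(1.286) = .901.

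**2. Success on either end point, each at two-sided .05.**

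| Correlation | Two-sided family-wise error | False claim of benefit (one-sided .025 each) |
|---|---|---|
| 0 (independent) | 1 − .95² = .0975 | 1 − .975² = .049 |
| .5 (assumed) | .091 | .045 |
| .7 (assumed) | .083 | .042 |

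The correlated rows are bivariate-normal calculations. The upper bound is .05 + .05 = .10 two-sided. The right-hand column is to be read against a nominal .025.

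**3. Success on both end points, each at .05.** The error does not exceed .05, but joint power cannot exceed the lower of the two powers. For hospital stay at 30 per group, two-sided .05, normal approximation: power = Φ(d·√15 − 1.960).

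- d = 0.5: .49
- d = 0.8: .87
- d = 0.84: .90

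Under independence, joint power is .90 × hospital-stay power: .45, .72 or .81 for assumed hospital-stay power of .50, .80 or .90.

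**4. Splitting alpha (Bonferroni, .025 each).** By the article's formula, POPF power at 30 per group falls to Φ(3.246 − 2.241) = .842. Power of .90 needs .34875 × (2.241+1.282)²/.1225 = 35.3, so 36 per group (72 in total). With Fisher's exact test, power falls from .893 to .827. With an uncorrected chi-square test, exact power falls from .943 to .903.

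**5. POPF as sole primary, or POPF first and hospital stay only if POPF is significant.** POPF is tested at the full .05, so the family-wise error stays .05, POPF power stays .90 and the size stays 30 per group.

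**The case against.** The strongest reply is that POPF is plainly the confirmatory end point. The objective, the hypothesis in the Introduction, the formal hypotheses, the sample size and the aim restated in the Discussion all concern it alone. No sentence says that hospital stay alone would count as success, and none requires both. Testing order is commonly left to an analysis plan, which is not at hand, and the article condenses a fuller protocol. This stands in part: a reader might infer that the error is already inflated, or that the power claim has already failed, and the documents do not support either inference. A POPF-first reading preserves both .05 and .90. What remains is a fault in the stated text. Two outcomes carry the primary label without ranking, and only one has a hypothesis and a sample size. An analysis plan could add an order, but the end-point section and the abstract would still present two equal primaries.

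A second reply is that .0975 overstates the risk. It counts errors in both directions and assumes independence, whereas the hypotheses are directional and the article itself describes a longer stay as a consequence of POPF. That is correct, which is why the one-sided figures and the correlated cases are shown.

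A reader might also infer that splitting alpha costs almost nothing. The .903 that suggests this holds only for the uncorrected chi-square test, which the article does not name. The article's own formula gives .842.

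Finally, discharge decided by an unblinded team is a separate weakness. The Limitations section already acknowledges lack of blinding and possible detection bias, and a testing order would not cure it.

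**Conclusion.** The concern holds in conditional form. The sample size of 30 per group is correct for POPF alone. The fault is a second primary end point with no stated inferential role. Unless POPF is tested first or made the sole primary, there are two cases:

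- **Either suffices:** the two-sided family-wise error can reach about .10, or about .049 against .025 for false claims of benefit. Positive correlation lowers these figures.
- **Both required:** the .90 does not describe joint success, and the true joint power cannot be known from the article.

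The correlations and hospital-stay effects are assumptions. Severity is should-fix: the POPF analysis is not invalidated and the repair is small. In a 60-patient study allocated by patient choice, nominal alpha is not the main threat to inference.

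**What to change.** Name POPF the single primary end point in the Primary End Points section and in the abstract. Make postoperative hospital stay the first key secondary end point, tested at .05 only if POPF is significant. State that the .05 is two-sided, since the hypotheses are worded in one direction but 30 per group reproduces only at two-sided .05.

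The cost is a dated wording amendment to the protocol, and to the registry entry if it lists the same two primaries, made before outcomes are compared. No patients are added, and alpha .05, POPF power .90 and 30 per group are unchanged. The downside is that no stand-alone primary claim can be made on hospital stay. If the sponsor wants to keep that claim, splitting alpha equally would need 36 per group by the article's own formula to hold .90 for POPF, and hospital stay would need its own hypothesis and sizing.

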#### Secondary End Points

The secondary end points are intra-abdominal infection, incision infection, and postoperative treatment costs.

### Definitions

In this study, POPF will be identified using the definition proposed by the International Study Group of Pancreatic Surgery [21]. Intra-abdominal infection and incision infection will be evaluated on the basis of the Common Terminology Criteria for Adverse Events (CTCAE) version 5.0. Severe adverse events are events rated grade 3 or higher using CTCAE. Postoperative hospital stay refers to the interval from the day of surgery to discharge. Postoperative treatment costs encompass all hospitalization expenses incurred from the patient’s return to the ward after surgery until discharge, measured in yuan renminbi.

### Patient Eligibility

#### Inclusion Criteria

The inclusion criteria were as follows.

Patients aged between 18 and 75 years.Patients scheduled to undergo distal pancreatectomy (including the body and tail of the pancreas) with the intended pancreatic transection line located on the left side of the portal vein.Patients who fully understand this study, agree to participate in it voluntarily, and sign the informed consent form.

#### Exclusion Criteria

The exclusion criteria were as follows.

Patients with a history of previous pancreatic surgery.Patients requiring additional surgical procedures for the residual pancreas.Patients with proximal pancreatic duct obstruction and planned anastomosis between the residual pancreas and the digestive tract.Patients using long-acting somatostatin analogues during the perioperative period.Patients who are judged by the investigator to be unsuitable for participation in this study.

### Group Allocation

Patients will be allocated to the experimental or control group according to their choice. Recruitment for either group will be discontinued upon reaching the predefined sample size.

### Study Interventions

#### Surgical Approach

The laparoscopic approach will be prioritized for all enrolled patients. Open conversion will be initiated upon the surgeon’s judgment of laparoscopic feasibility.

#### Evaluation of the Texture of the Pancreas

After the baseline visit and admission, eligible participants will be classified by the surgeon and the first assistant in terms of the texture of the pancreas (soft, medium, hard) during the operation. In case of disagreement between the surgeon and first assistant, a third surgeon will be invited to make the decision.

#### Ligation of the Pancreatic Stump for the Experimental Group

The pancreas will be ligated 5 mm from the pancreatic stump before or after severing the pancreas. To achieve proper ligation force, a predetermined force will be generated with a force device outside the body, and the deformation length of the implantable silicone/rubber will be recorded. When performing ligation in vivo, the specific ligation force will be reproduced by reproducing the deformation length measured in vitro. In this study, the ligation force will be provided by a 3.2-mm-diameter silicone ring composed of silicone and barium sulfate (Gnovo Inc). As shown in Figure 2, this silicone ring will be stretched to 15 mm, generating an applied force of 1.3 N, and the tension will be transmitted to 2 strands of size-0 braided nonabsorbable silk suture (Ethicon, Inc) during pancreatic stump ligation. No additional ligation of MPD will be performed.

**Figure 2 figure2:**
[figure not shown]
The silicone ring and the nonabsorbable silk suture used for the ligation of the pancreatic stump.

#### Pancreatic Stump Management for the Control Group

The stapler technique will be the preferred method for pancreatic transection. No additional ligation of MPD will be performed. When surgeons determine that stapler use is unsuitable for a particular patient, the pancreatic stump will be managed by manual suturing. Selective ligation of the MPD will be contingent upon its identification following pancreatic transection.

#### Distal Pancreatectomy

Distal pancreatectomy will be performed according to the standard process.

#### Postoperative Management

General clinical treatment will be conducted in both groups. The patient’s body temperature and drainage volume will be recorded daily. The amount of amylase concentration in the drainage fluid as well as the blood will be routinely measured. Drains will not be removed before postoperative day 3. After postoperative day 3, drains will be left in place until the amylase concentration is less than 3 times the upper limit of normal serum amylase concentration, the output is less than 20 mL/day with an amylase concentration less than 3000 U/L, or the output is less than 5 mL/day.

#### Follow-Up

For 3 months after surgery, patients will be required to undergo regular follow-up assessments every 2 weeks through outpatient or telephone consultations. The following information will be collected during each follow-up assessment: basic information and the general condition of the patient, whether the patient has been extubated (if the patient has not been extubated, the recent drainage condition will be recorded), and recent medical interventions. Laboratory tests and imaging examinations will be performed at the surgeon’s discretion.

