### Ethical Considerations

This study was approved by the ethics committee of Union Hospital, Tongji Medical College, Huazhong University of Science and Technology (approval 2024-0833-02). Written informed consent will be obtained from all patients prior to the initiation of study procedures. Participants aged 18 to 75 years will receive a comprehensive explanation of the study’s background, objectives, methodology, potential benefits, risks, and any possible inconveniences. Their rights as research participants will also be clearly outlined. All questions will be addressed thoroughly by the research team to ensure full understanding before consent is given. Participation in this study is entirely voluntary. Consent forms must be signed by the participant, or in cases involving minors or individuals unable to provide consent, by a parent or legally authorized representative. A model informed consent form has been provided and uploaded in Multimedia Appendix 2. This study will be conducted in accordance with the approved protocol and the ethical principles set forth in the current version of the Declaration of Helsinki. All participants were provided with surgical accident insurance. The research team will cover all the treatment costs for study-related complications as assessed and approved by the ethics committee. The data collected in this study will be de-identified. The results will be submitted for publication in an international peer-reviewed journal with anonymized data.

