### Limitations

One of the primary limitations of this study is its nonrandomized controlled design. Since this study investigates a novel pancreatic stump management technique that has not yet undergone large-scale clinical validation, the institutional ethics committee recommended an enrollment approach based on patient choice to ensure patient autonomy. Furthermore, the involvement of 2 distinct surgical techniques precluded blinding of the investigators. These factors may introduce performance and detection biases into the study. On the basis of the findings of this investigation, the research team will evaluate the need for subsequent randomized controlled clinical trials to address these methodological constraints. The relatively small sample size is another limitation of this study. The inherent variability among the included cases may prevent confirmation of the study hypothesis. We will make a data-driven decision regarding potential sample size expansion.

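### Follow-up testing for POPF is left to an unblinded surgeon, and the plan treats masking as ruled out although masked, rule-based coding of the end point is feasible

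*Protocol article*

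**What the plan says.** All references are to the protocol article.

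- **Primary End Points:** "The primary end points are POPF and postoperative hospital stay". The alternative hypothesis is directional: a lower POPF rate with ligation.
- **Definitions:** "POPF will be identified using the definition proposed by the International Study Group of Pancreatic Surgery". No assessor is named.
- **Postoperative Management:** care is described as common to the two groups, with temperature and drain output charted each day. On amylase it says: "The amount of amylase concentration in the drainage fluid as well as the blood will be routinely measured", with no days given. Every drain stays in until at least postoperative day 3, and removal after that follows numeric amylase and output criteria.
- **Follow-Up:** contacts every two weeks for three months, in clinic or by telephone, collecting drain status and recent medical interventions each time. Beyond that, "Laboratory tests and imaging examinations will be performed at the surgeon’s discretion".
- **Limitations:** "the involvement of 2 distinct surgical techniques precluded blinding of the investigators". The section concedes that performance and detection bias may follow, and leaves the remedy to a possible later randomized trial.
- **Group Allocation:** patients choose their group.

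**The concern.** Whether a POPF is recorded depends partly on whether someone looks for it and partly on who decides that the findings meet the definition. In follow-up, the decision to test rests with a surgeon who knows the technique. This is a stated rule, and following it faithfully can give different testing intensity in the two groups. If ligation patients are tested less, or borderline findings in them are read more leniently, their observed POPF rate falls without any true effect, in the direction of the hypothesis.

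The bias-control steps that the article describes are stratification by pancreatic texture, a logistic model for risk factors and an upper age limit. They address who is in each group, not how the outcome is found or coded.

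The Limitations section draws too wide a conclusion from its premise. Two visibly different techniques prevent masking of the operators. They do not prevent someone from coding POPF on data that do not show the technique, and most of those data are already collected: amylase, daily output, drain status and interventions.

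**Working it through.** **1. The plan's own figure.** Inputs from Sample Size Calculation: control rate 0.40, ligation rate 0.05, type I error .05, power .90. The mean rate is (0.40 + 0.05)/2 = 0.225.

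n = 2 × 0.225 × 0.775 × (Zα + Zβ)² / 0.35²

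- Two-sided: (1.960 + 1.282)² gives n = 29.91, rounded up to 30. This reproduces the stated 30 per group.
- One-sided: (1.645 + 1.282)² gives n = 24.38, rounded up to 25. This does not.

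Two-sided .05 is therefore the right basis for the illustration.

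**2. Where detection is common to both groups and where it is not.**

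| Stage | Stated source of information | Left open |
|---|---|---|
| In hospital | Daily output, routine amylase, drain in to at least day 3, numeric removal criteria | Amylase days |
| Follow-up | Two-weekly contact with drain status and interventions | Laboratory tests and imaging, at discretion |
| Classification | Named published definition | Who applies it, and whether masked |

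**3. Effect of unequal detection.** Assumptions, none of them from the documents: no true difference, true POPF rate p in both groups, all control events detected, a fraction s of ligation-group events detected. Ligation count ~ Binomial(30, p·s); control count ~ Binomial(30, p). Sum the joint probability over all pairs of counts where the Pearson test is significant at two-sided .05 and favours ligation.

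| s | p = 0.30 | p = 0.40 |
|---|---|---|
| 1.0 | 2.4% | 2.4% |
| 0.9 | 4.3% | 4.9% |
| 0.8 | 7.4% | 9.0% |
| 0.7 | 12.0% | 15.8% |

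Fisher's exact test at p = 0.40 gives 1.3%, 2.8%, 5.6% and 10.5% in the same order.

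**4. A scenario closer to the stated rule.** Discretion governs only follow-up tests. Suppose 25% of events depend on them and half of those are missed in the ligation group. Then s = 1 − 0.25 × 0.5 = 0.875, and the chance is 5.0% (p = 0.30) to 5.7% (p = 0.40), about twice the 2.4%.

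**5. How much one classification matters.** With 12/30 in control, 5/30 with ligation gives Pearson p = .045 and 6/30 gives p = .091.

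**6. Upper bound on the claim.** To turn a true 40% in both groups into an observed 40% versus 5%, the fraction missed in the ligation group would have to be 1 − 0.05/0.40 = 87.5%.

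**The case against.** The strongest reply has four parts.

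- **In-hospital detection is not discretionary.** A reader might infer from the follow-up sentence that POPF as a whole is looked for at the surgeon's discretion. The document does not support that. Postoperative Management describes common care, daily output, routine amylase and numeric drain criteria. This part of the reply stands and narrows the concern.
- **The classifier is not named.** A reader might infer that the unblinded operating team classifies POPF. The article says that investigators are unblinded, not who codes the end point. Naming the adjudicator and the amylase days is detail that an article may leave to the full protocol, so their absence is not the finding. What the article does state is that testing is discretionary and that blinding was precluded.
- **Money.** A reader might see a motive to under-record in the statement that "The research team will cover all the treatment costs for study-related complications". The same sentence makes this subject to assessment and approval by the ethics committee, so it does not support that reading and carries no weight here.
- **The weakness is disclosed, and the size is assumed.** Both are true. Disclosure, however, rests on a reason that reaches only the operators. The detection fractions are illustrative, and applying them to every ligation-group event is harsher than a rule that covers follow-up alone; step 4 of the working shows the milder case.

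**Conclusion.** The point holds in a limited form. Follow-up tests for a primary end point are at the discretion of a surgeon who knows the group, and the article treats detection bias as unavoidable when part of it is not. The exposure is mainly in follow-up testing and in classification.

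Under the stated assumptions, the false-positive chance in favour of ligation rises from 2.4% to 4%-5%, 7%-9% or 12%-16% as detection in the ligation group falls to 90%, 80% or 70%. It is 5%-6% if only a quarter of events depend on discretionary tests and half of those are missed. The documents do not say which fraction applies, and they do not show that detection will in fact differ.

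A reader might go further and conclude that ascertainment alone could produce the planned contrast. It could make a result significant, but 40% versus 5% would need seven in eight ligation-group events to go unrecorded, and nothing in the article suggests that. This is an inexpensive improvement worth making, not an error that invalidates the design.

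**What to change.** **Definitions and Statistical Analysis.** Derive POPF for the primary comparison by a written rule that follows the definition already named. Apply it to a listing with group and stump technique removed, holding drain and serum amylase, daily output, drain duration and recorded interventions. Include an amylase value from a day common to both groups while every drain is still in. Have it coded by existing study personnel who did not operate, or by program, and lock it before group is merged in.

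**Analysis of follow-up events.** Keep every event that meets the definition in the primary analysis. Report the number of discretionary laboratory and imaging tests per patient by group. Add a sensitivity analysis that excludes events found only by such tests. They should not be dropped from the primary comparison: that would lose true events while keeping interventions that unblinded clinicians choose.

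**Scope.** Limit the masked rule to POPF. This listing is too thin to grade intra-abdominal infection by CTCAE.

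**Limitations.** Reword to say that operators cannot be masked but end-point coding is.

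**Cost.** Wording, a masked listing and possibly a few added assays on the common day. The sample size stays at 30 per group, and no treatment or drain rule changes. Masked coding does not remove differences in who was tested or treated, nor confounding from patient choice; the count of tests by group only makes the first of these visible.
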